### **6.4.3 Distribution of Participants**

- The number of participants screened, randomized, and completed the trial will be listed for the overall study and each center to determine the three analysis datasets (FAS, PPS, SS).
- The number and proportion of participants screened, participants who failed screening, and reasons for failure will be listed for the overall study and each center.

### **6.4.4 Demographic Data and Baseline Analysis**

Analysis will be based on the actual data in the FAS.

Descriptive statistics for demographic data and other baseline characteristics:

- For continuous variables that follow a normal distribution, the number of cases, mean, and standard deviation will be calculated; for those that do not follow a normal distribution, the number of cases, median, and quartiles will be calculated.
- For categorical and ordinal data, the frequency and proportion will be calculated.
- Inferential statistical results (p-values) will be listed as descriptive results.

### **6.4.5 Medication Adherence and Concomitant Medication Analysis**

#### **6.4.5.1 Medication Adherence Analysis**

- The percentage of participants with medication adherence within the range of 80%-120% will be calculated, and differences between groups will be compared using the chi-square test or Fisher's exact test.
- Medication exposure will be compared between groups using the t-test.
- A table will be used to describe the actual medication intake, prescribed medication intake, and medication adherence of participants.

#### **6.4.5.2 Concomitant Medication Analysis**

- Concomitant medications will be coded using World Health Organization (WHO) Drug and summarized according to the first level of Anatomical Therapeutic Chemical Classification System (ATC) classification, with the number of cases and proportions calculated.
- A list of concomitant medications will be provided.

### **6.4.6 Efficacy Analysis**

#### **Primary Efficacy Endpoint Analysis:**

The difference between the breast pain VAS score at eight week and the baseline value will be analyzed using Analysis of Covariance (ANCOVA), with treatment group and center as fixed effects, and baseline value as a covariate. Missing values will be imputed using the LOCF method. Both PPS and FAS analyses will be conducted. Changes in breast pain VAS score from baseline at weeks 4, 8, and 12 (1 month after discontinuation of treatment) will be compared between groups using mixed-effects model for repeated measures (MMRM), with the model including treatment group, visit, group-by-visit interaction, and baseline value as a covariate. Missing values will not be imputed.

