## **3 Study Design**

A randomized, double-blind, placebo-controlled, multicenter clinical study design will be adopted, and it is expected to be conducted concurrently at ten research centers across the country.

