### 6.2 Sample Size Estimation

Based on the literature (Jiangsu Journal of Traditional Chinese Medicine, 2021, 53(8): 3 and Journal of Traditional Chinese Medicine, 2019(17): 5), the reduction in breast pain VAS score after two menstrual cycles of treatment with Danlu capsule is 3.2 points, while the reduction in the control group (placebo) is approximately 1.5 points, with a standard deviation of 3.4 points. The sample size for this superiority trial was calculated using a t-test. Based on a superiority margin of 0, a two-sided  $\alpha$  of 0.05, and  $\beta$  of 0.05 (power = 95%), with 1:1 allocation, the required sample size per group was determined to be 105 using PASS 21.0 software. Considering a dropout rate of 20%, the sample size is increased to 132 cases per group, resulting in a total of 264 cases.

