#### **Secondary Efficacy Endpoint Analysis:**

(1) Quality of life scale (SF-36) Score Changes at weeks 4, 8, and 12 (one month after discontinuation of treatment):

Group differences will be compared using MMRM, with the model including treatment group, visit, group-by-visit interaction, and baseline value as a covariate. Missing values will not be imputed. The analysis will be based on the actual data in the FAS.

(2) Anxiety and depression assessment scale score changes at weeks 4, 8, and 12 (one month after discontinuation of treatment):

Group differences will be compared using MMRM, with the model including treatment group, visit, group-by-visit interaction, and baseline value as a covariate. Missing values will not be imputed. The analysis will be based on the actual data in the FAS.

(3) Breast lump size changes at weeks 4 and 12 (one month after discontinuation of treatment):

Group differences will be compared using MMRM, with the model including treatment group, visit, group-by-visit interaction, and baseline value as a covariate. Missing values will not be imputed. The analysis will be based on the actual data in the FAS.

(4) Hormonal regulation indicators (serum estrogen, progesterone, prolactin) changes:

Group differences will be compared using the Wilcoxon test. The analysis will be based on the actual data in the FAS.

(5) Cytokine (IL-6, TNF- $\alpha$ ) changes:

Group differences will be compared using the Wilcoxon test. The analysis will be based on the actual data in the FAS.

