| Mean±SD                     | XX.XX±XX.XX             | XX.XX±XX.XX           |
| Change from baseline        |                         |                       |
| N (NMissing)                | XXX                     | XXX                   |
| Mean±SD                     | XX.XX±XX.XX             | XX.XX±XX.XX           |
| LS mean (SE)                | XX.XX (XX.XX)           | XX.XX (XX.XX)         |
| LS mean difference (95% CI) | XX.XX (XX.XX~XX.XX)     |                       |
| P-value                     | XX.XX                   |                       |
| 8 week                      |                         |                       |
| N (NMissing)                | XXX                     | XXX                   |
| Mean±SD                     | XX.XX±XX.XX             | XX.XX±XX.XX           |
| Change from baseline        |                         |                       |
| N (NMissing)                | XXX                     | XXX                   |
| Mean±SD                     | XX.XX±XX.XX             | XX.XX±XX.XX           |
| LS mean (SE)                | XX.XX (XX.XX)           | XX.XX (XX.XX)         |
| LS mean difference (95% CI) | XX.XX (XX.XX~XX.XX)     |                       |
| P-value                     | XX.XX                   |                       |
| 12 week                     |                         |                       |
| N (NMissing)                | XXX                     | XXX                   |
| Mean±SD                     | XX.XX±XX.XX             | XX.XX±XX.XX           |
| Change from baseline        |                         |                       |
| N (NMissing)                | XXX                     | XXX                   |
| Mean±SD                     | XX.XX±XX.XX             | XX.XX±XX.XX           |
| LS mean (SE)                | XX.XX (XX.XX)           | XX.XX (XX.XX)         |
| LS mean difference (95% CI) | XX.XX (XX.XX~XX.XX)     |                       |
| P-value                     | XX.XX                   |                       |

Note: Mixed-effects model for repeated measures (MMRM) was used to compare between-group differences, with the model including treatment group, visit, group-by-visit interaction, and baseline value as a covariate. Missing values were not imputed.

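### The primary ANCOVA adjusts for center but every MMRM omits it and fixes one baseline slope across visits, so MMRM intervals may be somewhat wider than needed and the two week-8 VAS estimates use different covariates

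*Supplement*

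**What the plan says.** The trial is multicenter; SAP section 3 states that "it is expected to be conducted concurrently at ten research centers across the country".

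Section 6.4.6 describes two analyses of VAS change in one paragraph:
- Week-8 ANCOVA (the primary analysis): "with treatment group and center as fixed effects, and baseline value as a covariate". For this model, "Missing values will be imputed using the LOCF method".
- MMRM over weeks 4, 8 and 12: "with the model including treatment group, visit, group-by-visit interaction, and baseline value as a covariate". For this model, "Missing values will not be imputed".

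The secondary part of 6.4.6 repeats the MMRM specification for SF-36, the anxiety and depression scales and lump size: "Group differences will be compared using MMRM, with the model including treatment group, visit, group-by-visit interaction, and baseline value as a covariate". The notes to Tables 4-3 to 4-19 carry the same four terms, including those for lump size score and consistency score. The note to the VAS MMRM tables, for example, reads "with the model including treatment group, visit, group-by-visit interaction, and baseline value as a covariate. Missing values were not imputed".

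The model is thus stated in full each time. Center and baseline-by-visit appear in none of these statements, and the SAP does not explain why the ANCOVA and the MMRMs differ. It gives no center variance and does not say whether randomization is stratified by center. No protocol is available to settle that.

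**The concern.** By adjusting the primary model for center, the sponsor treats center as relevant. The MMRM tables cover VAS, three lump measures, eight SF-36 domains and four psychological scales. Patient-rated scales and operator-dependent ultrasound are outcomes where centers may plausibly differ. If they do, and the arms are balanced within centers, leaving center out keeps that variance in the residual. The reported standard errors are then too large and the tests conservative.

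The single baseline slope raises a smaller matter. It assumes that baseline predicts change equally at weeks 4, 8 and 12, so the week-8 contrast is not adjusted with a week-8 slope as it is in the ANCOVA.

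Tables 4-1 and 4-3 will both show a week-8 VAS difference in the FAS. If the two disagree, the reader cannot tell how much comes from covariates and how much from LOCF.

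**Working it through.** **Inputs from SAP sections 3 and 6.2.** Ten centers; reductions of 3.2 and 1.5 points (difference 1.7); SD 3.4; two-sided alpha 0.05; power 95%; 105 per group, raised to 132 per group (264 in total) for 20% dropout.

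**Plan's own figure.** Normal approximation: n = 2 × (1.960 + 1.645)² × 3.4² / 1.7² = 104. With the noncentral t, 104 per group gives power 0.9483 and 105 gives 0.9501, so 105 is reproduced. Then 105 / 0.80 = 131.25, rounded up to 132 per group, 264 in total. The sample size stands; its SD and N are used below.

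**Center.** The center share of residual variance (ICC) is not in the documents, so a range is assumed. Approximate week-8 95% half-width:
- Without center: t × 3.4 × √(4/264) = 1.969 × 3.4 × 0.1231 = 0.824.
- With center, arms balanced within centers: replace 3.4 by 3.4 × √(1 − ICC) and use 9 fewer degrees of freedom.
- With center, allocation not balanced by center: multiply further by √(263/254).

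| Assumed ICC | With center, balanced | Half-width without center / with center | With center, not balanced | Half-width without center / with center |
|---|---|---|---|---|
| 0 | 0.824 | 1.000 | 0.839 | 0.983 |
| 0.01 | 0.820 | 1.005 | 0.834 | 0.988 |
| 0.05 | 0.803 | 1.026 | 0.817 | 1.008 |
| 0.10 | 0.782 | 1.054 | 0.796 | 1.036 |
| 0.15 | 0.760 | 1.084 | 0.773 | 1.066 |

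With 210 participants instead of 264 the balanced ratios are the same. Without balance, break-even is near ICC = 1 − 254/263 = 0.034. With balance, the nominal 5% test without center has size 2 × (1 − Φ(1.96/√(1 − ICC))), which is 4.4% at ICC 0.05 and 3.4% at 0.15.

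**Simulation check.** 60 replicates per scenario; N = 264, ten centers; baseline SD 1.5; between-visit residual correlation 0.6; unstructured covariance; 10% random dropout after week 4 and a further 10% after week 8 (all assumed). With balanced arms, the mean week-8 standard error without and with center was 0.4182 and 0.4104 at ICC 0.05 (ratio 1.019), and 0.4164 and 0.3976 at ICC 0.10 (ratio 1.047). This agrees broadly with the table.

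**Baseline-by-visit.** Week-8 standard error without and with the term, in the same simulation:
- equal slopes: 0.4208 and 0.4211;
- slopes −0.3/−0.6/−0.5: 0.4211 and 0.4200;
- slopes −0.2/−0.8/−0.5: 0.4095 and 0.4052.

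The change is about 0-1%.

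**Agreement of the two week-8 estimates.** Averaged over replicates, MMRM estimates with and without the extra terms agreed within about 0.01 point, so no bias appears. ANCOVA with LOCF differed from the MMRM by 0.07-0.12 point on average, which reflects LOCF. Within a single trial the covariates can matter as much. With allocation not balanced by center, the difference between center-adjusted and unadjusted estimates has an SD of about 0.08 point at ICC 0, 0.12 at 0.05, 0.15 at 0.10 and 0.17 at 0.15.

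**The case against.** The strongest reply is that little follows from the omission.

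- **Precision.** A reader might infer that the MMRM intervals are certainly too wide. The documents do not support that. It needs an appreciable center variance and balance within centers, and neither is stated. At ICC near zero without balance, adding center makes intervals slightly wider. This stands, and the point is therefore put as a possibility.
- **Relevant ICC.** The outcomes are changes adjusted for baseline, which already removes part of any stable center difference. For example, if follow-up regresses on baseline with an assumed slope of 0.5, half of a constant center offset is removed, or three quarters of its variance (1 − 0.5²). This stands, and it favors the lower end of the ICC range.
- **Role of the MMRM.** A reader might infer that a check on the primary result has been compromised. Section 6.4.2 gives the robustness check to multiple imputation; the MMRM tables are titled as comparisons over time. No designated check fails.
- **Like for like.** Aligning covariates leaves LOCF against no imputation. This stands. Alignment removes only one of the two sources of disagreement.
- **Baseline-by-visit.** The documents do not show that slopes differ by visit, and the simulated gain is at most about 1%. It is a refinement only.

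What the reply does not answer is why center belongs in the primary model and not in the MMRM specified in the same paragraph.

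**Conclusion.** The concern holds in limited form. Every MMRM leaves out the center term that the sponsor's primary model includes, and every one imposes a common baseline slope, without explanation. The possible loss, assuming arms balanced within centers, is 0-3% in interval width for a center share of 0-0.05 and 5-8% for 0.10-0.15. These shares are assumptions, and the half-widths come from a two-group approximation using the SD in section 6.2. Any error in test size under balance is conservative.

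A reader might go further and infer bias or a weakened primary result. Neither is supported: the randomized comparison is not biased by the omission, and the primary ANCOVA already adjusts for center. This is a low-cost improvement to the supporting and secondary analyses.

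**What to change.** Before database lock, add center as a fixed effect to all MMRMs in section 6.4.6 and in the notes to Tables 4-3 to 4-19, to match the primary ANCOVA. Add baseline-by-visit as a minor refinement. If center is left out on purpose, state why.

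Cost: a wording change and about 11 more fixed-effect parameters (9 for ten centers, 2 for three visits; 10 for the lump tables, which show two post-baseline visits) against 264 planned participants. If center variance is near zero and allocation is not balanced by center, intervals become up to about 1-2% wider. The report should also say that the two week-8 VAS estimates still differ in missing-data handling.

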#### **Secondary Efficacy Endpoint Analysis:**

(1) Quality of life scale (SF-36) Score Changes at weeks 4, 8, and 12 (one month after discontinuation of treatment):

Group differences will be compared using MMRM, with the model including treatment group, visit, group-by-visit interaction, and baseline value as a covariate. Missing values will not be imputed. The analysis will be based on the actual data in the FAS.

(2) Anxiety and depression assessment scale score changes at weeks 4, 8, and 12 (one month after discontinuation of treatment):

Group differences will be compared using MMRM, with the model including treatment group, visit, group-by-visit interaction, and baseline value as a covariate. Missing values will not be imputed. The analysis will be based on the actual data in the FAS.

(3) Breast lump size changes at weeks 4 and 12 (one month after discontinuation of treatment):

Group differences will be compared using MMRM, with the model including treatment group, visit, group-by-visit interaction, and baseline value as a covariate. Missing values will not be imputed. The analysis will be based on the actual data in the FAS.

(4) Hormonal regulation indicators (serum estrogen, progesterone, prolactin) changes:

Group differences will be compared using the Wilcoxon test. The analysis will be based on the actual data in the FAS.

(5) Cytokine (IL-6, TNF- $\alpha$ ) changes:

Group differences will be compared using the Wilcoxon test. The analysis will be based on the actual data in the FAS.

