#### (5) Cytokines

Levels of interleukin-6 (IL-6), tumor necrosis factor-alpha (TNF- $\alpha$ ), and other cytokines will be measured before and after treatment to assess changes.

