| Indicator                           | Treatment group
(N=XXX) | Placebo group
(N=XXX) | Total (N=XXX)     |
|-------------------------------------|----------------------------|--------------------------|-------------------|
| Estrogen (pg/ml), median (IQR)      | XX.X (XX.X, XX.X)          | XX.X (XX.X, XX.X)        | XX.X (XX.X, XX.X) |
| Progesterone (nmol/L), median (IQR) | XX.X (XX.X, XX.X)          | XX.X (XX.X, XX.X)        | XX.X (XX.X, XX.X) |
| Prolactin (ng/ml), median (IQR)     | XX.X (XX.X, XX.X)          | XX.X (XX.X, XX.X)        | XX.X (XX.X, XX.X) |
| IL-6 (pm/ml), median (IQR)          | XX.X (XX.X, XX.X)          | XX.X (XX.X, XX.X)        | XX.X (XX.X, XX.X) |
| TNF- $\alpha$ (pm/ml), median (IQR) | XX.X (XX.X, XX.X)          | XX.X (XX.X, XX.X)        | XX.X (XX.X, XX.X) |

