#### 7.4.5 Sex Hormones

Table 4-20 Temporal analysis of measured values of estradiol (pg/ml) (full analysis set, FAS)

| Visit    | Treatment group (N=XXX) | Placebo group (N=XXX) |
|----------|-------------------------|-----------------------|
| Baseline |                         |                       |

| Visit                    | Treatment group (N=XXX) | Placebo group (N=XXX) |
|--------------------------|-------------------------|-----------------------|
| N (NMissing)             | XXX                     | XXX                   |
| Median (IQR)             | XX.XX (XX.X, XX.X)      | XX.XX (XX.X, XX.X)    |
| 8 week                   |                         |                       |
| N (NMissing)             | XXX                     | XXX                   |
| Median (IQR)             | XX.XX (XX.X, XX.X)      | XX.XX (XX.X, XX.X)    |
| Change from baseline     |                         |                       |
| N (NMissing)             | XXX                     | XXX                   |
| Median (IQR)             | XX.XX (XX.X, XX.X)      | XX.XX (XX.X, XX.X)    |
| Between-group difference |                         |                       |
| Median (IQR)             | XX.XX (XX.X, XX.X)      |                       |
| P-value                  | XX.XX                   |                       |

Note: Between-group differences were compared using the Wilcoxon test.

Table 4-21 Temporal analysis of measured values of progesterone (nmol/L) (full analysis set, FAS)

| Visit                    | Treatment group (N=XXX) | Placebo group (N=XXX) |
|--------------------------|-------------------------|-----------------------|
| Baseline                 |                         |                       |
| N (NMissing)             | XXX                     | XXX                   |
| Median (IQR)             | XX.XX (XX.X, XX.X)      | XX.XX (XX.X, XX.X)    |
| 8 week                   |                         |                       |
| N (NMissing)             | XXX                     | XXX                   |
| Median (IQR)             | XX.XX (XX.X, XX.X)      | XX.XX (XX.X, XX.X)    |
| Change from baseline     |                         |                       |
| N (NMissing)             | XXX                     | XXX                   |
| Median (IQR)             | XX.XX (XX.X, XX.X)      | XX.XX (XX.X, XX.X)    |
| Between-group difference |                         |                       |

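### Hormone and cytokine changes are tested without baseline adjustment: the Wilcoxon test is valid but less efficient than log or rank ANCOVA unless the baseline correlation is high

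*Supplement*

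**What the plan says.** SAP section 6.4.6 lists the hormones under "4) Hormonal regulation indicators (serum estrogen, progesterone, prolactin) changes" and the cytokines in the item after it. For both it states "Group differences will be compared using the Wilcoxon test", on the actual data in the FAS. The shells in 7.4.5 and 7.4.6 (Tables 4-20 to 4-24) show baseline, week 8 and change as median (IQR), then a between-group difference and a P-value. Each carries the note "Between-group differences were compared using the Wilcoxon test". No covariate is named and no confidence interval is planned.

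Baseline is available for all five markers. Table 2-4 summarises it (for example "Estrogen (pg/ml), median (IQR"), and section 5.1.2 plans hormone and cytokine measurements before and after treatment.

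The other efficacy comparisons adjust for baseline. The primary ANCOVA is fitted "with treatment group and center as fixed effects, and baseline value as a covariate". For SF-36, the anxiety and depression scales and lump size the text reads "Group differences will be compared using MMRM, with the model including treatment group, visit, group-by-visit interaction, and baseline value as a covariate". The MMRM for pain over time has the same terms. The SAP gives no reason for treating the five markers differently.

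**The concern.** A change score uses baseline in one fixed way: it subtracts all of it. Regression subtracts only the part that predicts week 8. With equal variances at the two visits that part is the baseline-to-week-8 correlation, rho. When rho is well below 1, full subtraction adds baseline noise to the outcome and the comparison loses precision.

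Section 1 names the mechanism of action among the things not yet clarified, and these five markers are the plan's direct biological evidence on it. They have no stated power. If the test is inefficient, a null result says less than it could. Low correlation is plausible for estradiol and progesterone, because the SAP ties sampling to no menstrual-cycle phase (no protocol is shown, so a rule may exist there). Skew may explain the choice of a rank test, but a log or rank ANCOVA handles skew and adjusts for baseline as well.

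**Working it through.** **The plan's own figure.** The only sample size stated is for pain (section 6.2): reductions 3.2 and 1.5, so difference 1.7; SD 3.4; two-sided 0.05; power 95%. The normal approximation gives n = 2 × (1.960 + 1.645)² × 3.4² / 1.7² = 104 per group, and the t-test gives 104.93, so 105. With 20% dropout, 105 / 0.8 = 131.25, so 132 per group and 264 in total. The figure reproduces. I use 105 per arm below, which is about what 20% dropout leaves of 132.

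**Inputs not in the documents (assumed).** Correlation rho from 0 to 0.9; log-normal markers with log-SD 0.7; log shift 0.28, that is a ratio of exp(0.28) = 1.32 and a standardised effect of 0.28 / 0.7 = 0.40. Center is not simulated.

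**Closed form, normal or log scale.** In units of the outcome variance:
- variance of change = 2(1 − rho)
- residual variance of ANCOVA = 1 − rho²
- efficiency of change relative to ANCOVA = (1 − rho²) / [2(1 − rho)] = (1 + rho) / 2
- the Wilcoxon test multiplies this by 0.955 under normality

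| rho | Efficiency of Wilcoxon on change | Information lost |
|---|---|---|
| 0 | 0.48 | 52% |
| 0.3 | 0.62 | 38% |
| 0.5 | 0.72 | 28% |
| 0.7 | 0.81 | 19% |
| 0.9 | 0.91 | 9% |

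Example at rho 0.2. For Wilcoxon on change, SE = √1.6 × √(2 / (105 × 0.955)) = 0.179; 0.40 / 0.179 − 1.96 = 0.28; power 61%. For ANCOVA, SE = √0.96 × √(2 / 105) = 0.135; 0.40 / 0.135 − 1.96 = 1.00; power 84%.

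**Simulation with skewed markers.** Wilcoxon on raw change against rank ANCOVA (ranked week 8 on ranked baseline) and ANCOVA on logs. The figures come from separate runs of 1,500 to 2,000 or more trials per setting, which agree to within about two points.

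| rho | Wilcoxon on change | Rank ANCOVA | Log ANCOVA |
|---|---|---|---|
| 0.2 | 61% | 83% | 84% |
| 0.4 | 75% | 86% | 89% |
| 0.6 | 86% | 93% | 95% |
| 0.7 | 95% | 97% | 98% |
| 0.8 | 99% | 100% | 100% |
| 0.9 | 100% | 100% | 100% |

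These are for a rise in the marker. For a fall of the same log size the gap to rank ANCOVA is wider: 51% vs 82% (rho 0.2), 63% vs 86% (0.4), 80% vs 93% (0.6), 90% vs 97% (0.7).

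**Validity.** With no effect, all three methods reject in about 5% of trials.

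**Choice of scale.** Raw-scale ANCOVA is not a safe replacement. With log-SD 1.0, a shift of 0.4 log-SD and rho 0.7 it has 81% power against 86% for the Wilcoxon test, while log ANCOVA has 98% and rank ANCOVA 97%.

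**The case against.** The plan can be defended on several grounds. The text and the table notes agree with each other. The markers are summarised as median (IQR), so skew was evidently expected, and a rank test is a recognised and valid answer to skew. Mechanism appears only in the background; the stated objective is efficacy and safety. These are the last two of five groups of secondary endpoints. All of that stands, and it limits the point to efficiency.

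Some stronger readings are tempting, but the documents do not support them:

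- *Most of the power is lost.* This needs low correlation. The SAP gives no rho, SD, effect size or power target for these markers, and at rho 0.8 or above almost nothing is lost.
- *Baseline is ignored and chance imbalance is left alone.* The tested variable is change, so baseline enters by subtraction. An imbalance is over-corrected, not ignored.
- *Participants with extreme baselines dominate the result.* Ranks limit their leverage. In the setting used here, Wilcoxon on raw and on log change had the same power to within a point (59% vs 58% at rho 0.2, 73% vs 73% at 0.4, 88% vs 88% at 0.6). The loss comes from the subtraction.
- *Leaving out center is a special inconsistency.* The MMRMs omit center too; only the primary ANCOVA has it.
- *Changing the test costs nothing.* Rank ANCOVA gives no estimate in the marker's units, and log ANCOVA gives a ratio, so the result would no longer be the median change that the shells display.

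**Conclusion.** The point holds as one of efficiency, not validity. The five marker comparisons forgo a baseline adjustment that the SAP makes in every other between-group efficacy model, with data it already collects. The cost runs from about half the information at rho 0 to about a tenth at rho 0.9. In the log-normal setting with a rise of 32% that is roughly 22 power points at rho 0.2 (83% − 61%), 11 at 0.4 (86% − 75%), 7 at 0.6 (93% − 86%) and next to none at 0.8 or above. The sizes rest on an assumed log-SD, shift and correlation. The direction does not depend on which rho below 1 is taken: log and rank ANCOVA did at least as well as the Wilcoxon test in every setting tried. The primary analysis, its conclusion and the sample size are untouched.

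**What to change.** In section 6.4.6 (4) and (5), make ANCOVA on log week-8 values the main between-group comparison, with treatment group, log baseline and center (as in the primary model). Report the ratio between groups with its 95% CI. Specify rank ANCOVA (ranked week-8 values on ranked baseline and center) for any marker where the log scale proves unsuitable, and state in advance how that will be decided. Do not use ANCOVA on the untransformed scale.

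Change both the bodies and the notes of Tables 4-20 to 4-24, so that the P-value belongs to the effect shown. Keep the medians (IQR) and the Wilcoxon test on change as supportive.

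The cost is revised SAP wording, five table shells and slightly more programming; no new data are needed. The price in interpretation is that the main effect becomes a ratio and not a median change in the original units. Section 1 says the SAP will be finalised before database lock, so the change should be made before then.
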